### Interventions, duration and frequency of follow-up

The acute KRT pathway will consist of two specific interventions:Monitoring, reporting and audit of acute KRT KPIs.Provision of individualized prescriber and program reports for acute KRT initiation patterns.

The acute KRT care pathway will be implemented in a stepwise fashion with a pilot followed by randomized stepped wedge roll out at centres across Alberta over the subsequent 21 months. Roll out of ICUs will be performed in clusters and will coincide with individual site activation of a novel, province-wide electronic provincial clinical information system (CIS), Connect Care (EPIC, Verona WI).

#### Monitoring and reporting of acute KRT KPIs

The monitoring, reporting and audit of acute KRT KPIs will be done by means of automatically generated reports delivered directly to KRT stakeholders at each ICU at quarterly intervals (Table 2). These unit-level aggregate summaries of KPIs will be benchmarked to other ICUs in Alberta and will be delivered in an electronic fashion. KPIs captured in the reports for CKRT will include: 1) filter life, 2) downtime, 3) delivered dose, 4) ultrafiltration realized and 5) number of access alarms; and for IKRT: 1) treatment completion, 2) delivered dose, 3) solute clearance, 4) ultrafiltration realized and 5) catheter malfunction.

**Table 2 Tab2:** Intervention definitions and parameters - Key Performance Indicators (KPIs)

**CRRT KPI**	**Operational Definition**	**Proposed Benchmark**
Filter Life	Average number of hours of filter life of all filters per quarter	> 50% of filters last 72 hours
Downtime	Time CRRT not running per day/ Each day of CRRT prescription	< 15%
Delivered Dose	Actual delivered dose in ml/Kg/h / Prescribed dose in ml/Kg/h	> 85% of dose and between 25 and 30 ml/Kg/h
Ultrafiltration Realized	Ultrafiltration realized per 24 hours/ Ultrafiltration prescribed per 24 hours	> 85%
Access Alarms	Number of alarms recorded per machine per day of therapy	< 5 alarms/d
**IRRT KPI**	**Operational Definition**	**Proposed Benchmark**
Treatment Completion	Number of IRRT treatment completed/ Total number of IRRT treatments	100%
Treatment Time	[Delivered – Prescribed hours of dialysis therapy]/ Prescribed hours of dialysis therapy	> 85% of time
Solute Clearance	Percentage difference between serum urea pre-treatment and serum urea post treatment	> 10% decrease/treatment
Ultrafiltration Realized	Ultrafiltration realized for treatment/ Ultrafiltration prescribed per treatment	> 85%
Catheter Malfunction	Number of IRRT runs with catheters reversed/ Number of IRRT runs	< 20%

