### Primary outcomes

Measurement of change across acute KRT KPIs that will include the following:∘ CKRT: 1) filter life, 2) downtime, 3) delivered dose, 4) ultrafiltration realized and 5) number of access alarms∘ IKRT: 1) treatment completion, 2) delivered dose, 3) solute clearance, 4) ultrafiltration realized and 5) catheter malfunctionNumber of appropriate acute KRT initiationsNumber of patients entering maintenance KRT programsAcute KRT and healthcare systems costs

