APACHE II Score	number
SOFA score	number
Invasive/non-invasive ventilation	hrs/min
Vasopressors (include type)	hrs/min
CRRT/IHD/SLED	hrs/min
Cumulative daily fluid balance prior to RRT	mls
Creatinine, urea, pH, bicarbonate, potassium on day of RRT initiation	result
Renal Recovery at ICU Discharge	y/n - IHD
Renal Recovery at Hospital Discharge	y/n – IHD/PD
Renal Recovery at 6 Months	y/n - IHD/PD
ICU Mortality	A/D
Hospital Mortality	A/D
6-month Mortality	A/D
ICU length of Stay	days
Hospital Length of Stay	days
Number of admissions to site	aggregate
Patient days	aggregate
Ventilator days	aggregate
RRT days	Days CRRT/IHD/SLED
CRRT and IRRT data - filter life, reasons for retiring filters, treatment time lost, prescription/dose, machine alarms, machine down times, type of coagulation, blood flow rates, filtration fraction, adverse events, solute clearance, ultrafiltration realized	aggregate
Economic data - cost of filters, fluids, anticoagulation medications, RRT catheters, patient life-years gained, quality of life adjusted years (QUALY), re-hospitalizations, recurrence/chronic RRT, health care provider related costs	aggregate
QOL and PROMs	aggregate

Data sources will include multiple Alberta Health Services administrative databases, the Nephrology Information System (NIS) and the Patient Based Renal Information System (PARIS) (Supplementary Table 1) [20, 21].

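### Table 2 sets two KPIs against benchmarks on a different scale (IKRT Treatment Time and CKRT Filter Life), and the IKRT delivered-dose KPI named as primary has no row there

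*Protocol article*

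**What the plan says.** Table 2, in the section on monitoring and reporting of acute KRT KPIs, gives each KPI an operational definition and a proposed benchmark.

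- **IKRT Treatment Time.** The definition is "Delivered – Prescribed hours of dialysis therapy]/ Prescribed hours of dialysis therapy", with the opening bracket just before the first word. The benchmark is more than 85% of time.
- **CKRT Filter Life.** The definition is "Average number of hours of filter life of all filters per quarter". The benchmark is "> 50% of filters last 72 hours".
- **Neighbouring rows.** CKRT Delivered Dose is "Actual delivered dose in ml/Kg/h / Prescribed dose in ml/Kg/h" and IKRT Ultrafiltration Realized is "Ultrafiltration realized for treatment/ Ultrafiltration prescribed per treatment". Both are plain ratios with an 85% threshold.

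The first primary outcome is "Measurement of change across acute KRT KPIs that will include the following". Its intermittent list begins "IKRT: 1) treatment completion, 2) delivered dose, 3) solute clearance". The text above Table 2 gives the same list. Table 2 has no IKRT delivered-dose row; Treatment Time stands in that position.

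Under Methods/design, unit teams are to work on practices that miss their KPI benchmarks, using the quarterly reports.

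**The concern.** A benchmark is usable only if the KPI is computed on the scale in which the benchmark is expressed. Two rows of Table 2 break that rule. Treatment Time is a signed deviation from prescription, centred on zero, but is held to a threshold that suits a ratio centred on one. Filter Life is a mean in hours, held to a criterion on a proportion of filters, which is in effect a condition on the median.

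The reports are generated automatically and the benchmarks tell units where to direct effort, so a row that nearly always fails, or is judged on the wrong summary, sends the wrong signal. If a programmer or a site quietly corrects the row, the KPI reported is no longer the one published. The naming mismatch adds to this: the IKRT delivered dose listed as primary has either no definition in the article or, by position, the faulty one.

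**Working it through.** The plan gives no worked example for either KPI, so there is no figure of its own to reproduce. The inputs are the definitions and benchmarks in Table 2. The filter lifetimes below are constructed for illustration.

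**Treatment Time.** Let D be delivered hours and P prescribed hours. The written KPI is (D - P)/P = D/P - 1.

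| D/P | Score as written | Above 85% as written? | D/P above 85%? |
|---|---|---|---|
| 0.50 | -50% | no | no |
| 0.84 | -16% | no | no |
| 0.85 | -15% | no | no |
| 0.86 | -14% | no | yes |
| 1.00 | 0% | no | yes |
| 1.85 | 85% | no | yes |
| 1.90 | 90% | yes | yes |

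A pass needs D/P - 1 > 0.85, so D > 1.85 P. On an illustrative 4 h prescription that is more than 1.85 × 4 = 7.4 h. Reversing the sign does not help: (P - D)/P > 0.85 requires D < 0.15 P, so only runs that were almost wholly missed would pass. The plain ratio D/P, the form of the neighbouring rows, works with the stated threshold.

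**Effect on estimated change.** The two scales differ by the constant 1, which cancels in any before/after difference. Illustration: D/P of 0.80 and 0.82 before (mean 0.810), and 0.90 and 0.93 after (mean 0.915), gives a change of 0.105. As written, the means are -0.190 and -0.085, and the change is again 0.105.

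**Filter Life.** Ten filters in each example:

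| Lifetimes | Mean | Share reaching 72 h | Benchmark |
|---|---|---|---|
| four at 120 h, six at 60 h | (480 + 360)/10 = 84 h | 40% | fail |
| six at 72 h, four at 17 h | (432 + 68)/10 = 50 h | 60% | pass |
| four at 72 h, six at 71 h | (288 + 426)/10 = 71.4 h | 40% | fail |
| six at 72 h, four at 1 h | (432 + 4)/10 = 43.6 h | 60% | pass |

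The last two rows show that the conflict remains if no filter runs beyond 72 h (an assumption). In each pair the unit with the higher mean fails and the one with the lower mean passes.

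**KPI names.** The second IKRT item is delivered dose in the text above Table 2 and in the primary outcomes, but Treatment Time in Table 2. No section links the two.

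**The case against.** The strongest reply is that the primary outcome is change in the KPIs, analysed by interrupted time series, and not attainment of a benchmark. That stands. As shown, change in Treatment Time is identical on either scale, and change in mean filter hours can be estimated, although it does not show movement towards the benchmark. A reader might infer that the primary analysis is spoiled; the article does not support that. It also plans to assess KPIs in aggregate, but does not say that the aggregate rests on benchmark attainment.

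Second, the benchmarks are labelled as proposed, and reports also compare each unit with other Alberta ICUs. That comparison survives both mismatches. It does not remove the stated use of KPI benchmarks in feedback.

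Third, Treatment Time is probably a drafting slip, since the benchmark wording and the neighbouring rows point to a ratio. The Filter Life benchmark can likewise be scored directly from filter-level lifetimes. Both are fair, and they make the repair easy, but nothing in the article makes the correction.

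Two further inferences are tempting and should not be drawn:

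- **Filters removed when therapy ends are counted as failures.** Table 2 does not say so, and a mean classifies nothing as a failure. Table 4 lists "reasons for retiring filters" among the data, and handling rules may sit in the full plan.
- **CKRT courses are so short that many filters must end with therapy.** The 2019 figures give 3278 × 24/1278 = 61.6 h per patient if all 1278 patients had CKRT. That is the low end. If 398 patients had only IKRT (one per IKRT patient-day, an extreme assumption), it is 78,672/880 = 89.4 h. Neither average shows why filters ended.

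**Conclusion.** The point holds as an inconsistency within Table 2, and between Table 2 and the KPI lists. Treatment Time as written can exceed its threshold only when delivery is above 1.85 times prescription, so literal coding flags essentially every unit every quarter. This is pure algebra and needs no assumption about the data. Filter Life as defined cannot be scored against its benchmark from the mean alone; the constructed examples are enough to prove that.

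How often the mean would mislead in practice depends on the lifetime distribution, which the documents do not give. Assuming a mean of 72 h, the share reaching 72 h would be 36.8% under an exponential distribution (exp(-1)), 45.6% under a Weibull with shape 2, and about 51% with shape 4. An exponential unit would need a mean of 72/ln 2 = 103.9 h to reach 50%. These figures are illustrations only.

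The consequence is wrong feedback against benchmarks and an unclear identity for one primary KPI. It is not bias in the estimated pre/post change.

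**What to change.** 1. Define Treatment Time as delivered hours divided by prescribed hours, matching the neighbouring ratio rows, so that it is on the scale of its benchmark.
2. Use one name and one definition for the second IKRT KPI in Table 2, the text above it and the primary outcomes. Alternatively, define an IKRT delivered dose in its own row and say how Treatment Time relates to it.
3. Put Filter Life and its benchmark on the same scale, for example by reporting the proportion of filters reaching 72 h with mean hours as descriptive. If the mean stays as the KPI, the authors need to express the benchmark in hours.

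Survival analysis of filters, with rules for elective removals and clustering by patient, is an optional refinement and is not needed to remove the mismatch.

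The cost is two table rows, one consistent name and a matching change in the report code, best made before the reports are coded. One practical check remains: Table 4 lists the filter data as aggregate, so the 72 h share must be counted at source or filter-level times retained.

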**Fig. 2 Fig2:**
[figure not shown]
Outline of learning health system knowledge to action framework. The healthcare system data are used to set local priorities for improvement. Data on priority problems and potential contributors help find the evidence based solutions to improve local health systems (data to knowledge). Using evidence based knowledge, this will inform local quality improvement and implementation science guided efforts (knowledge to performance). Finally, the continuous monitoring of local KPIs and practices will develop practice based knowledge while revealing future opportunities for quality improvement (performance to data). Adapted from Kilbourne et al. [16]

Dialyzing Wisely will utilize a structure-process-outcome framework for quality assessment by implementing a standardized framework to each acute KRT program (Fig. 3) [17, 18]. Each participating ICU will be structured to be led by a team with expertise in KRT (e.g., physician, educator, registered nurse, administrator) who will undergo and further disseminate targeted education strategies prior and during the intervention. Each ICU will receive quarterly performance reports on a minimum suite of essential KPIs tailored to their unit’s specific practice. Through this feedback the team members will work on adjusting and improving KRT practices that do not meet KPI benchmarks. Further, acute KRT prescribers will receive individualized reports outlining their prescription practices and their alignment with best evidence. Follow up with individual ICUs and practitioners will occur to better understand and evaluate prescribing practices. After completion of the intervention period, the impact of the intervention will be measured through select clinical and economic outcome measures (e.g., mortality, lengths of stay, KRT utilization and renal recovery). At this time, using our partners (outlined below) we will transition ownership to local stakeholders.

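### Table 2 defines IKRT Treatment Time as a relative difference but benchmarks it as a fraction delivered, so a fully delivered run scores 0% against a target above 85%

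*Protocol article*

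**What the plan says.** In the protocol article, section *Monitoring and reporting of acute KRT KPIs*, the Treatment Time row of Table 2 (IRRT block) has the operational definition "Delivered – Prescribed hours of dialysis therapy]/ Prescribed hours of dialysis therapy", with an opening bracket before the first word. The proposed benchmark in the same row is more than 85% of time.

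The other delivered-versus-prescribed rows are plain ratios. CRRT Delivered Dose is "Actual delivered dose in ml/Kg/h / Prescribed dose in ml/Kg/h", with a benchmark that includes more than 85% of dose. IRRT Ultrafiltration Realized is "Ultrafiltration realized for treatment/ Ultrafiltration prescribed per treatment", with a benchmark of more than 85%. The CRRT Ultrafiltration Realized row has the same form and limit.

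The indicators go out in "automatically generated reports delivered directly to KRT stakeholders at each ICU at quarterly intervals". *Methods/design* says that teams will use this feedback for "adjusting and improving KRT practices that do not meet KPI benchmarks".

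The running text of the monitoring section, and again *Primary outcomes*, list the IKRT indicators as "1) treatment completion, 2) delivered dose, 3) solute clearance, 4) ultrafiltration realized and 5) catheter malfunction". Treatment Time is in neither list, and Table 2 has no IRRT row called delivered dose.

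**The concern.** A benchmark of more than 85% of time reads naturally as the share of prescribed time that was delivered. The printed definition is instead a signed relative difference, whose value under perfect delivery is zero. Taken together, the two cells describe a target that correct delivery cannot meet.

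This matters because reporting against benchmarks is itself part of the intervention. *Knowledge translation and dissemination* directs targeted education at indicators that perform poorly. An indicator that marks correct delivery as failing would send that effort after a deficit that does not exist. *KPI and interrupted time series analysis* also plans to assess the indicators in aggregate. If that aggregate counts benchmarks met, this component would be stuck at not met before and after implementation.

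**Working it through.** **Inputs.** D = delivered hours and P = prescribed hours. The definition and the 85% benchmark come from the Treatment Time row of Table 2. The article gives no prescribed run length, so P = 4 h is assumed for illustration only; it cancels out of the result.

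**Algebra.** As printed, the indicator is (D − P)/P = D/P − 1.

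- Full delivery: D = P gives 1 − 1 = 0%.
- Any short run: D < P gives a negative value.
- Passing: D/P − 1 > 0.85 means D > 1.85 P, for any P.

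**Worked values for P = 4 h.**

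| Delivered | D/P | As printed, D/P − 1 | Printed score above 85%? | Plain ratio above 85%? |
|---|---|---|---|---|
| 3.20 h | 80% | −20% | no | no |
| 3.40 h | 85% | −15% | no | no (limit is strict) |
| 3.44 h | 86% | −14% | no | yes |
| 3.60 h | 90% | −10% | no | yes |
| 4.00 h | 100% | 0% | no | yes |
| 7.40 h | 185% | +85% | no (limit is strict) | yes |
| 7.44 h | 186% | +86% | yes | yes |

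As printed, every run from 0% to 185% of prescribed time fails.

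**Other readings of the row.**

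- *Absolute difference*, |D − P|/P: a perfect run scores 0% and fails, while a run not delivered at all scores 100% and passes.
- *Shortfall*, (P − D)/P: a perfect run scores 0% and fails, and only runs delivering under 15% of prescribed time pass.
- *Target met in more than 85% of runs*: this would need a per-run tolerance for the difference, and the row gives none.
- *Plain ratio*, D/P: a perfect run scores 100% and passes. Of the forms tried, only this one makes the benchmark workable.

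**Same limit on the two scales.** D/P > 0.85 is equivalent to D/P − 1 > 0.85 − 1 = −0.15, that is, above −15%.

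**Effect on the planned analysis.** *Statistical analyses* uses ARIMA interrupted time-series models for change in indicator performance. Write R for a unit's mean of D/P in a period. The printed form gives R − 1. A change from R1 to R2 is (R2 − 1) − (R1 − 1) = R2 − R1, the same as for the plain ratio. Level changes, slopes and differences between ICUs are therefore identical, and so is the order of the ICUs. Only comparison with the fixed benchmark is damaged.

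**The case against.** The strongest reply is that this is a slip in one cell and that its intent is visible from the benchmark wording and the neighbouring ratio rows. No report specification is shown, automatic generation does not mean coding word for word from an article table, and roll-out begins with a pilot in which a score of 0% for every full run would probably be noticed. All of this stands. It makes the harm in the reports conditional, but it does not remove the contradiction, which no other part of the article corrects.

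A reader might infer more than the article supports, in four ways:

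- *That the trial could show no effect on this indicator.* The article names no endpoint for Treatment Time defined as the proportion meeting the benchmark. The stated outcome is change in the indicators, and that change is the same under either formula.
- *That every ICU would certainly be shown as failing each quarter.* This assumes that the printed formula is coded unchanged.
- *That the formula is proven to be the wrong cell.* The ratio rows make that likely. However, Table 2 also has a shortfall-type indicator with a complementary limit (Downtime, below 15%), so the mismatch could lie in the benchmark cell. The article establishes a conflict, not which side is at fault.
- *That Treatment Time is a stated primary outcome.* It is the IRRT row left over once the other four are matched to the listed indicators, so it probably fills the delivered dose slot, but this is an inference.

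**Conclusion.** The definition and benchmark of IKRT Treatment Time contradict each other. This follows from the two cells alone: full delivery scores 0%, and passing needs more than 1.85 times the prescribed time. A misreading of the PDF is unlikely, because the bracketed subtraction over a repeated denominator is the usual form of a relative difference.

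The consequence is limited to one of the ten indicators in Table 2. If the reports follow the printed formula, units delivering IKRT as prescribed would be flagged as below benchmark, feedback on this indicator would be misdirected, and a count of benchmarks met, alone or within an aggregate, would be uninformative for it. The interrupted time-series estimate for the indicator's value (analysed untransformed) and the peer comparison are unaffected. The row should be corrected before the reports are built, but it does not threaten the planned estimate of change.

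**What to change.** Reconcile the two cells of the Treatment Time row, keeping the document's own threshold. The most plausible correction is to define the indicator as delivered hours divided by prescribed hours, in line with the other ratio rows, and leave the benchmark at more than 85%. Equivalently, keep the difference and state the same limit as above −15%. Confirm which form the report specification uses.

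In the same edit, make the names agree: either rename the Table 2 row or change the delivered dose entry in the IKRT lists under *Monitoring and reporting of acute KRT KPIs* and *Primary outcomes*, so that it is clear which measure is reported and analysed.

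The cost is one table row, one label and at most one line of report code. It needs no new data and does not affect patients.

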**Prescriber Report Metrics**		
**RRT Initiation Criteria**		**Benchmarks**^**a**^
Serum potassium		> 6.0 mmol/L
pH		< 7.20
Serum bicarbonate		< 12 mmol/L
Oxygenation status		Impaired oxygenation as per P/F ratio of < 200
Cumulative volume status		Cumulative Fluid Balance defined as > 10% positive fluid balance^b^ anchored from time of ICU admission

^a^Benchmarks obtained from STARRT-AKI inclusion criteria

^b^Cumulative Fluid Balance is calculated as (fluid intake – fluid output in liters since ICU admission) / (weight in kilograms) × 100%

#### Prescriber reporting

An ICU-specific prescriber and program report will be provided to each prescriber and ICU on a quarterly basis. The report will include: 1) the number of acute KRT initiations, 2) acute KRT initiations based on conventional indications (i.e., hyperkalemia, acidosis, metabolic status, oxygenation status and cumulative fluid status) termed ‘appropriate initiations’, 3) general guidelines of KRT initiation criteria as per STARRT-AKI standard initiation arm protocol. (Table 2) [5] These will be benchmarked against prescriber patterns from providers in the same ICU, as well as similar ICUs across Alberta.

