## Background

Acute kidney replacement therapy (KRT) is a core life support technology used in approximately 10–12% of critically ill patients [1]. It is generally used to support patients with overt kidney failure or as part of a broader strategy for multi-organ support in ICU settings, along with mechanical ventilation and vasoactive medications. Its utilization has expanded, with recent estimates showing growth of more than 10% per year [2, 3]. Acute KRT in the ICU can be delivered intermittently (i.e., intermittent kidney replacement therapy [IKRT]) or continuously (i.e., continuous kidney replacement therapy [CKRT]) depending on the available technology.

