### Acute KRT in Alberta

In 2019, acute KRT was initiated in 1278 patients across 18 adult ICUs in Alberta, which represents 5–8% of our critically ill population. This coincides with 3278 KRT patient-days of continuous KRT and 398 intermittent KRT patient-days with estimated direct healthcare costs of $764–865 per day and $528 per day, respectively [3, 4]. Non-adherence to evidence-based practice may have led to an additional 56 patients per year with new end stage kidney disease (ESKD) [5]. These survivors of critical illness complicated by severe AKI, who are now receiving maintenance dialysis after hospital discharge, have attributable healthcare costs exceeding $100,000 annually per patient [6, 7]. These costs do not include associated travel and lost work time costs as well as significant impairments in the quality of lives of these patients. Strategies are needed to standardize and reduce variations in care, improve patient centered outcomes, improve health system efficiencies and reduce patient and health care system costs.

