### Data management

Effects of prescriber and acute KRT program patterns in the initiation of acute KRT will be determined by monitoring resource use associated with initiation of KRT at both a program level and healthcare system level. This will be done by determining first the units of each resource and then by assigning costs to each unit. At the program level we will capture the number of acute KRT initiations as well as total patient-days of acute KRT per specific modality (i.e., intermittent or continuous). These acute KRT initiations will also be adjusted for severity of illness to enable translation across units with varying case-mix, acuity and workload. Acute KRT disposable costs will include KRT filters, catheters, replacement and anticoagulation solutions.

New intake of critically ill survivors with severe AKI into ESKD dialysis programs will be reviewed on a quarterly and yearly basis to determine any changes relevant to use of this resource to the Alberta healthcare system. We will ensure that any changes in intakes reflect acute KRT initiations based on adherence to best-evidence practices.

Data will be collected on patient characteristics: (i.e., demographics, type of admission [medical, surgical, trauma]), clinical status (i.e., comorbid diseases including chronic kidney disease, primary diagnosis), acuity (i.e., APACHE II, SOFA, CFS), ICU treatment (i.e., duration of renal replacement therapy, mechanical ventilation, vasoactive therapy), ICU and hospital lengths of stay, and outcomes (i.e., renal recovery and mortality); and KRT-associated resource data: (i.e., filter use, prescription/dose, machine alarms/down time, anticoagulation, re-hospitalizations, progression of renal disease). Data variables to be captured are summarized in Table 4.

**Table 4 Tab4:** Data variables

Data Variable	Description
ICU location	admission ICU
Age	years
Sex:	M/F
Weight	kg
Date of Hospital Admission	dd/mm/yyyy
Date of ICU Admission (dd/mm/yyyy):	dd/mm/yyyy
Admission class	med/surg/neuro/trauma
ICU discharge location	unit/hospital
ICU Admission Diagnosis – cardiovascular, respiratory, gastrointestinal, genitourinary/renal, endocrinological/metabolic, neurological, trauma, burn, sepsis, surgery	yes/no
Co-morbidities – AIDS, chronic RRT, chronic heart failure, respiratory insufficiency, cirrhosis, diabetes mellitus, hepatic failure, immune suppression, leukemia, lymphoma, metastatic cancer, coronary artery disease	yes/no
Clinical Frailty Scale	number

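### A primary outcome counts appropriate KRT starts with no denominator, so it has no fixed direction of success and does not measure adherence to the initiation criteria

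*Protocol article*

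**What the plan says.** The Primary outcomes section lists, beside the KPIs, maintenance KRT entry and costs, the number of acute KRT initiations that are appropriate. It states no denominator.

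The Prescriber reporting section supplies the definition. A start is appropriate when it rests on a conventional indication, with criteria tabulated in Table 2. On content: "The report will include: 1) the number of acute KRT initiations, 2) acute KRT initiations based on conventional indications". On comparison: "These will be benchmarked against prescriber patterns from providers in the same ICU", and the sentence goes on to include similar ICUs in the province. Total and appropriate starts are thus both reported, but no proportion is defined.

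Three other places bear on the point:

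- Data management, on resource use: "These acute KRT initiations will also be adjusted for severity of illness to enable translation across units with varying case-mix, acuity and workload". Table 4 in the same section lists "Number of admissions to site".
- The ITS section plans ARIMA models that allow for temporal trends. The Health outcome measures section adds simple pre/post tests.
- The Healthcare system costs section expects the pathway to avert some acute KRT and to delay some.

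**The concern.** The prescriber reports aim to bring the decision to start KRT into line with the initiation criteria. If they work, the direct effect is fewer starts that meet no criterion. Those starts are, by definition, not part of the primary outcome. The outcome can respond only indirectly, and the sign of that response depends on whether the starts are averted or delayed and on how prescribers treat the remaining patients.

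This is the only primary outcome that looks at the initiation decision itself, and that decision is the target of one of the pathway's two interventions. A flat, rising or falling count could each accompany better adherence, so none of the three can be read as success or failure.

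**Working it through.** The article gives no target, effect size or baseline for this outcome, so there is no figure of the plan to reproduce. The check asks how the count and the proportion respond to the changes the article expects.

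**Inputs from the article**

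- Starts per year N = 1278: "In 2019, acute KRT was initiated in 1278 patients across 18 adult ICUs in Alberta". One start per patient is assumed.
- Growth in use: "recent estimates showing growth of more than 10% per year" (Background). 10% is used. It is a general estimate and not an Alberta forecast.
- Roll-out: 21 months, or 1.75 years.
- KRT patients are 5–8% of the critically ill population (Acute KRT in Alberta).

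**Assumed, because the article does not say**

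- Baseline share appropriate s = 60%, range 40–80%.
- Half of the inappropriate starts are affected.
- In scenario B, a quarter of those affected later meet a criterion and are started.
- In scenario C, appropriate starts themselves also fall by 10%.

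**Formulas**

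Appropriate A = N × s and inappropriate I = N − A. At s = 60%, A = 1278 × 0.60 = 767 and I = 511.

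- A (averted): count = A; proportion = A / (A + I/2). At 60%: 767 / (767 + 256) = 75%.
- B (some delayed): count = A + 0.25 × I/2. At 60%: 767 + 64 = 831, a rise of 8.3%; proportion = 831 / (831 + 256) = 76.5%.
- C (more conservative overall): count = 0.9 × A. At 60%: 690, a fall of 10%; proportion = 690 / (690 + 256) = 73.0%.
- D (no change in practice, growth only): count = A × 1.10^t; proportion = s. At 60%: 843 after one year and 767 × 1.10^1.75 = 906 after 21 months.

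| Scenario | s = 40%: count; proportion | s = 60%: count; proportion | s = 80%: count; proportion |
|---|---|---|---|
| Baseline | 511; 40% | 767; 60% | 1022; 80% |
| A | 511 (0%); 57.1% | 767 (0%); 75.0% | 1022 (0%); 88.9% |
| B | 607 (+18.8%); 61.3% | 831 (+8.3%); 76.5% | 1054 (+3.1%); 89.2% |
| C | 460 (−10%); 54.5% | 690 (−10%); 73.0% | 920 (−10%); 87.8% |
| D, 1 year | 562 (+10.0%); 40% | 843 (+10.0%); 60% | 1125 (+10.0%); 80% |
| D, 21 months | 604 (+18.2%); 40% | 906 (+18.2%); 60% | 1208 (+18.2%); 80% |

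In A, B and C the proportion rises every time, while the count is flat, up or down. In D the count rises although practice has not changed.

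Scenario C also shows a limit of the proportion: it does not reveal that appropriate starts fell. That is a reason to pair it with a rate and to keep the count as description.

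**Companion rate**

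If 1278 is 5–8% of the critically ill population, that population is 1278/0.08 = 15,975 to 1278/0.05 = 25,560. The 511 inappropriate starts are then 2.0 to 3.2 per 100 admissions, taking one admission per patient. Halving them gives 1.0 to 1.6, so averted starts become visible.

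**The case against.** **The word may be shorthand.** The same list names access alarms as a number, and Table 2 turns that into a rate per machine per day; treatment completion and catheter malfunction likewise become ratios there. A condensed article may leave the denominator to the full protocol. This is fair as far as it goes. But for initiations Table 2 gives only criterion thresholds, and no section supplies a denominator. As it stands, the outcome is a count. If the full protocol defines a proportion, the correction is one line.

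**Both figures are already reported.** Total and appropriate starts stand side by side in the prescriber report, so a recipient can form the fraction. That is true, and it makes the repair cheap. It does not change what the primary outcome is.

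**Trend and severity are handled.** ARIMA models can absorb smooth growth, so scenario D does not show that the planned main analysis is biased. Caseload matters mainly for the simple pre/post comparisons and for volume shifts that coincide with roll-out. Even there, a chi-square test on starts classed as appropriate or not would compare proportions. The severity adjustment mentions workload but belongs to resource use. Neither device can make an averted inappropriate start appear in a count of appropriate ones.

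**Stronger readings.** A reader might infer that the benchmarking compares caseload only, because the ICUs in Table 1 range from 5 to 32 beds. The article does not support this: comparison is within the same ICU and with similar ICUs, and total starts are shown. A reader might also infer that the third research question goes unanswered. It asks about patient-centred outcomes and costs, which maintenance KRT entry, costs, 90-day KRT dependence and mortality also address.

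**Conclusion.** The concern holds for the outcome as worded. A count of appropriate starts has no fixed direction of success and does not measure adherence to the initiation criteria. That conclusion follows from the definition and needs no assumed figure.

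The size is illustrative. With half of the inappropriate starts averted, the count does not change at all, while the proportion rises by 15 percentage points at an assumed baseline of 60% (17 points at 40%, 9 points at 80%). The baseline share, the halving, the conversion of delayed starts and the 10% fall are all assumptions.

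Sensitivity to caseload is a secondary weakness, limited to unadjusted comparisons and to shifts that coincide with roll-out. This is more than a missing detail, because the metric as stated could mislead. It does not undermine the other primary outcomes.

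**What to change.** 1. In Primary outcomes, define the initiation outcome as the proportion of acute KRT initiations that are appropriate: appropriate starts divided by all starts, with the number of starts as the denominator.
2. Pair it with inappropriate starts per 100 ICU admissions, using the admissions in Table 4, so that averted starts can be seen.
3. In the Prescriber reporting section, show each prescriber and ICU appropriate starts out of all starts, and benchmark that fraction.
4. Keep the raw count as a descriptive figure.

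The cost is wording in two sections and a change to the report template. Starts, their classification and admissions are already captured. The downside is that the proportion is imprecise where an ICU or prescriber has few starts, so the denominator should always be shown with it.
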